### **3.1 Rationale for Current Study**

Insulin resistance (IR) is a major factor responsible for Cardiometabolic risk and consists of two important features: peripheral and hepatic insulin resistance. Peripheral insulin resistance leads to decreased insulin stimulated glucose uptake in skeletal muscle and adipocytes as well as decreased insulin-mediated suppression of free fatty acids (FFA)-release. Hepatic insulin resistance increases plasma glucose levels by decreasing insulin mediated suppression of glucose production. The physiological mechanisms underlying insulin resistance are complex and not fully elucidated. Amongst others, an impairment of the skeletal muscle metabolic energy transduction pathways (mitochondrial dysfunction) has been suggested to be causally related to insulin resistance Mitochondrial and cytosolic fatty acid overload and incomplete fatty acid oxidation have been suggested to result in increased availability of fatty acids for lipid accumulation. Fatty acid metabolites are thought to induce insulin resistance in both liver and muscle by impairing the insulin-signaling pathway. Since T2 has been shown to activate processes enhancing fatty acid oxidation and thermogenesis, T2 could play a role in decreasing fat accumulation in muscle and liver and improve insulin sensitivity. Indeed TRC150094 has been shown to improve insulin sensitivity in preclinical studies. Whether TRC150094 will also improve insulin resistance in clinical studies remains to be elucidated. We therefore propose to investigate the safety and efficacy of treatment with TRC 150094 on increasing peripheral and hepatic insulin sensitivity as well as lowering muscle and liver triglyceride concentration in patients with the metabolic syndrome. The current Phase 2A study is designed to investigate safety and efficacy of TRC150094 for increasing insulin sensitivity in patients with increased cardiometabolic risk. This study will be a double-blind, randomized, placebo-controlled, multiple-dose, parallel study to assess effect on insulin sensitivity and to explore early efficacy markers (hepatic fat, lipid parameters and metabolic markers) after oral administration of TRC150094 tablet for 28 days. The tentative dose will be 50mg OD. This dose level has been calculated based on the assessment of safety and PK data obtained from SAD study. The exact dose level will be confirmed on the basis of interim safety and PK data obtained from MAD study. Full discussion of the study design is presented in Section 5.

#### **4. OBJECTIVES**

##### **4.1 Primary Objective**

To determine the safety and efficacy (in increasing insulin sensitivity) of TRC150094 once daily dosing for 4 weeks in male patients with increased cardiometabolic risk.

##### **4.2 Secondary Objectives**

- To evaluate the effect of TRC150094 on hepatic fat and metabolic parameters.
- To evaluate the ethnic differences for effect of TRC 150094 on Insulin sensitivity parameters

---

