## 5. STUDY DESIGN

### 5.1 Overview

This will be a Phase 2A, two-centre, double-blind, placebo-controlled, multiple-dose study to assess the effect of multiple oral doses of TRC150094 on insulin sensitivity in 40 overweight/obese male subjects. 20 Subjects will be enrolled in India and another 20 subjects at Amsterdam, the Netherlands. The maximum duration of participation in the study for each subject will be 17.5 weeks including a  $\leq 12$  weeks screening period, 4 weeks of treatment and a 10 days post treatment follow-up evaluation period (see Appendix B for Study Assessments).

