At each study site 20 subjects will be enrolled. Each subject will attend the study centre in a fasting state, for a screening visit, 2 study visits (one baseline and one end of treatment), 1 intermediate safety visit and 1 post-study follow-up visit (Total 5 visits). The subjects at each site will be randomized to receive TRC150094 or placebo in a ratio of 1:1. The tentative dose level is 50 mg to be administered OD (morning) under fasting conditions. Dosing will take place daily on Days 1–28. Subjects will arrive at the study centre for screening visit. Physical examination, vital signs, safety biochemistry and laboratory investigations for verification of inclusion/ exclusion criteria will be performed during screening visit. Subjects meeting all the inclusion criteria and none of the exclusion criteria and who have given their informed consent for the study will be asked to come for the study on Day 0 (or day -1 if required). Baseline investigations (including baseline clamp procedure and hepatic MRS) will be done on Day 0 (or day -1). Subjects will receive properly labelled bottle containing either Active treatment or Placebo as per the randomization number of the subject. Subjects will be asked to take the dose (tentatively 50mg) OD in the morning on Days 1-28 inclusive, in fasting conditions, with a glass of water. Drug compliance of at least 90% will be ensured. Hence the allowable limit of missing the dose should not be more than 3 days in total. Discontinuation should not be of more than 2 consecutive days at any point of time. Uniformity in timing of intake of medication will be advised which should be preferably within  $\pm 1$  hr of the time of intake of study medication on Day 1. Each subject will attend the study centre on Day 14 for safety investigations. A deviation of  $\pm 1$  day will be allowed for these visits. Subjects will attend the study centre again on Day 28 for clamp procedure and hepatic MRS. A

---

deviation up to +2 days is acceptable only in those cases that missed doses within the limits given above and has continued planned medication up to day of post-dose investigations. For further details, see Section 8.4 and Appendix A. It is planned that the study will take place over 6 months (including screening and follow-up periods).

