## **6. STUDY POPULATION AND TREATMENT**

### **6.1 Number and Description of Subjects**

It is intended that 40 subjects complete the study: 20 subjects in India and 20 subjects in Amsterdam, the Netherlands. An attempt will be made to dose 20 subjects at each study site (10 for Active treatment; 10 for Placebo treatment). Subjects will be identified by their initials. In addition, subjects will be given a screening number at screening and a subject (randomisation) number at the time of randomisation. A list identifying the subjects by initials, screening number, subject number and status (completed study/withdrawn) will be kept in the trial master file.

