### **6.2 Inclusion Criteria**

Subjects will be considered eligible for entry in the study if they meet all of the following criteria.

1. Adult male
2. Age range 30–65 years at screening
3. Caucasian or Indian Ethnicity
4. Waist circumference  $\geq 102$  cm for Caucasians and  $\geq 90$  cm for Indians at screening.
5. Fasting Serum Insulin  $\geq 10$  mU/ml at screening
6. Blood Pressure  $\geq 130/85$  mmHg at screening (or patients taking medication for hypertension)
7. Stable weight during 3 months prior to the study (assessed through medical history of the patient)
8. Drug naïve diabetic patients\* or patients with impaired fasting glucose i.e  $> 100$  mg/dl or  $5.5$  mmol/l and  $< 200$  mg/dl or  $11.0$  mmol/l. Diabetic patients who were taking metformin and have undergone washout for at least 4 weeks before Day 0 and are currently on life style modification as a treatment for diabetes will also be allowed in the study
9. Willingness to give written informed consent (prior to any study-related procedures being performed) and ability to adhere to the study restrictions and assessments schedule.

---

**\* Diabetic patient is defined as a patient with a documented history of type II DM or a documented history of a fasting glucose > 200 mg/dl or 11.0 mmol/l or 2x fasting glucose > 126 mg/dl or 6.9 mmol/l (2x = recorded twice)**

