#### **8.1.2 *Secondary study parameters/endpoints***

To determine the effect of TRC150094 on hepatic fat and multiple metabolic parameters

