arm. One catheter is used for sampling of arterialised blood using a heated hand box (60°C). The other catheter is used for infusion of [6,6-2H2]-glucose en and [1,1,2,3,3-2H2]-glycerol, glucose 20% and insulin. At t= -2hr, after drawing a blood sample for background enrichment of plasma glucose, a continuous infusion of [6,6-2H2]-glucose (>99% enriched, Cambridge Isotopes, Massachusetts, USA) is started at a rate of 0.11 µmol/kg per min after a priming dose equivalent to 100 min of infusion. After 1 hr, a continuous infusion of [1,1,2,3,3-2H2]-glycerol (>99% enriched, Cambridge Isotopes, Massachusetts, USA) is started at a rate of 0.11 µmol/kg per min after a priming dose of 1.6 µmol/kg/min. The first 2 infusion hrs are required for equilibration. After 115, 120 and 125 min blood samples are drawn for determination of glucose and glycerol enrichment to calculate basal endogenous glucose production and lipolysis, glucoregulatory hormones and FFA. Subsequently, the hyperinsulinemic clamp will start with a continuous infusion of insulin (Actrapid 100U/ml, Novo Nordisk ) for 2hr at a rate of 20mU/m^2 body surface area per min. Plasma glucose is measured every 10 min (Biosen C-line plus glucose analyzer; EKF Diagnostics, Barleben/Magdeburg, Germany at AMC, Netherlands; and YSI analyzer at Veeda Clinical Research India) and glucose 20% is infused at a variable rate to maintain plasma glucose at 5.0 mmol/l or 90 mg/dl. [6,6-2H2]-glucose is added to the 20% glucose solution to achieve glucose enrichments of 1% to minimize changes in isotopic enrichment due to changes in the infusion rate of exogenous glucose, and thus to allow for accurate quantification of endogenous glucose production and uptake. During the last 20 min of the hyperinsulinemic clamp, blood samples are drawn at 5 min intervals for determination of glucose and glycerol enrichment, glucoregulatory hormones and FFA. At t= 2.15hr, the infusion of insulin is increased to a rate of 60mU/m^2 body surface area per min. Plasma glucose is measured again every 10 min and enriched glucose 20% is infused at a variable rate to maintain plasma glucose at 5.0 mmol/l or 90 mg/dl. During the last 20 min of this insulin infusion step, blood samples are drawn at 5 min intervals for determination of glucose and glycerol enrichment, glucoregulatory hormones and FFA. Thereafter insulin infusion will be discontinued and participants will be offered a carbohydrate rich meal. The glucose infusion rate will be doubled. Plasma glucose levels will be measured every 10 minutes for the first hour. Thereafter blood glucose measurement will be done at 20 minute intervals or more frequently (at the discretion of the

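### The secondary objective on ethnic differences in drug effect can be estimated only as a difference between centres, so the result cannot be attributed to ethnicity

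*Protocol*

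**What the plan says.** Section 4.2, like the synopsis, lists as a secondary objective: "To evaluate the ethnic differences for effect of TRC 150094 on Insulin sensitivity parameters". The object of comparison is the drug effect, so the target is a difference between ethnic groups in active minus placebo.

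Recruitment is by country (5.1): "20 Subjects will be enrolled in India and another 20 subjects at Amsterdam, the Netherlands". Within each centre, "The subjects at each site will be randomized to receive TRC150094 or placebo in a ratio of 1:1", and 6.1 gives the cell sizes: "10 for Active treatment; 10 for Placebo treatment".

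The entry criterion in 6.2 reads "Caucasian or Indian Ethnicity" and does not assign either group to a centre. Other sections treat the two labels as interchangeable:

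- SIRT expression is for the Indian cohort in 8.4.3 and for Veeda subjects in Table 1 (8.7).
- 11.3 gives one blood volume for AMC subjects and another for Indian subjects.

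No section plans to enrol both groups at one centre, and none limits the objective to a comparison between centres.

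**The concern.** When each ethnic group comes from a single centre, anything at a centre that changes the size of the drug effect is inseparable from ethnicity. Examples are how the clamp is conducted, the glucose level achieved during it, local diet, and adiposity at entry. A larger or smaller effect in Ahmedabad than in Amsterdam would have several explanations that the data could not tell apart. The objective as worded invites the reader to choose one of them.

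This is a property of the objective and the recruitment plan. No later choice of analysis can undo it. What is at stake is a published statement about ethnicity and response to a new drug, resting on 20 subjects from each of two sites.

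**Working it through.** **1. The protocol's own figure.** Section 6.4 (repeated in 10.1) states 80% power with 20 per treatment group for a difference in Rd of 15 µmol/kg/min, SD 15, two-sided 0.05, Wilcoxon rank-sum test. By Noether's formula:

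- P(X<Y) = Φ(15/(15√2)) = 0.760
- total N = (1.960 + 0.842)² / (12 × 0.25 × 0.260²) = 38.6, which is 19.3 or 20 per group
- power at 20 per group = 81.4%

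The stated 80% reproduces. It applies to the treatment comparison pooled over centres. The protocol states no figure for the ethnic comparison.

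**2. What the design identifies.** There are four cells of 10: active and placebo in India, active and placebo in Amsterdam. Two quantities can be formed:

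- effect at a centre = mean change on active − mean change on placebo
- contrast = effect in India − effect in Amsterdam

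If all subjects in India are Indian and all in Amsterdam are Caucasian, the ethnicity indicator and the centre indicator are the same column. Treatment-by-ethnicity and treatment-by-centre are then one term. Enrolling more subjects in the same way does not separate them. The criterion in 6.2 would admit an Indian subject in Amsterdam, but a few such subjects would not remove the confounding.

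**3. Precision of the contrast.** Inputs: SD 15 (6.4), assumed to apply to the change in Rd in every cell; 10 per cell (6.1); 40 − 4 = 36 degrees of freedom.

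- variance of each centre's effect = 15² × (1/10 + 1/10) = 45
- variance of the contrast = 45 + 45 = 90, so SE = √90 = 9.5
- 95% half-width = 2.028 × 9.49 = 19.2 µmol/kg/min

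| True difference between centres in effect | Power (t, 36 df) |
|---|---|
| 7.5 | 12% |
| 15 | 34% |
| 22.5 | 64% |
| 30 | 87% |

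The difference detectable with 80% power is (1.960 + 0.842) × 9.49 = 26.6 by the normal approximation and 27.3 by non-central t, about 1.8 times the 15 used to size the trial. Detecting a difference of 15 with 80% power would take about 32 per cell, or 128 in all, and the result would still be a centre difference.

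The half-width scales with the SD: 2.028 × 10 × √(4/10) = 12.8 for SD 10, and 2.028 × 20 × √(4/10) = 25.7 for SD 20.

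**4. Why separate tests at each centre would mislead.** Suppose the true effect is 15 at both centres, so there is no difference at all. A simulated Mann-Whitney test with 10 per arm has power of about 51%. The chance that exactly one centre reaches significance is 2 × 0.51 × 0.49 = 0.50.

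**The case against.** The best defence has four parts.

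**Site differences largely cancel.** The objective concerns the effect, randomisation is balanced within each centre, and change from baseline is presented (10.3.2). A constant offset from a team or instrument largely drops out of active minus placebo. Tracer enrichment, endocrinology and metabolic markers for all 40 subjects are assayed at one laboratory (8.5.6), and the clamp procedure and glucose target are common to both sites (8.4.1). All of this stands. It limits the concern to features that change the size of the drug effect, but it does not remove those.

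**Some apparent confounders are not supported.** Section 8.4.1 names a different bedside analyser at each site ("YSI analyzer at Veeda Clinical Research India"), and a reader might infer that this alone biases the comparison. It would do so only if the achieved glucose level altered the drug effect. The different waist thresholds in 6.2 are deliberate ethnic criteria, not a site artefact, although they do make adiposity at entry a rival explanation. The scanner bears on hepatic fat, not on clamp results, and different bottle sizes leave the same once-daily dosing. Insulin is infused per body surface area while Rd is per kg, but the protocol gives no body sizes from which to judge any consequence.

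**The analysis may be in the statistical analysis plan.** A reader might infer from 8.1.2 ("To determine the effect of TRC150094 on hepatic fat and multiple metabolic parameters") that the objective has no endpoint, or from 10.3.2 that separate tests by site are intended. Neither holds: insulin sensitivity is already the main endpoint in 8.1.1 and in the synopsis, and no within-site test is planned in the protocol. The 50% figure above is a reason to rule such tests out, not evidence that they are planned.

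**Low power for a secondary contrast is normal in a Phase 2A trial of 40.** This is fair, and low power by itself would not justify a change. The attribution problem does.

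**Conclusion.** The point holds as a limit on interpretation. The treatment effect at each centre, and the difference between the two effects, can be estimated without bias from allocation. That difference cannot be attributed to ethnicity, because ethnicity and centre are in practice the same split. It will also be known only to about ±19 µmol/kg/min, with about 34% power for a difference of 15.

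The conclusion rests on two assumptions: that each centre supplies one ethnic group, which follows from how the protocol uses the labels and not from a stated rule; and that SD 15 applies to the change in Rd in each cell.

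It would go too far to say that the objective cannot be addressed at all: a descriptive between-centre comparison is available. The primary treatment comparison is unaffected.

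**What to change.** - Reword the objective in 4.2 and the synopsis, for example: *to describe the treatment effect on insulin sensitivity at each centre (Indian and Caucasian subjects)*.
- Report one treatment-by-centre estimate with its 95% interval: a difference of differences in change in Rd, or a rank-based equivalent consistent with 10.3.2. Do not infer a difference by comparing separate significance tests within each centre.
- State that any difference found is between centres or populations and will not be attributed to ethnicity.
- List any subject whose race, already recorded at screening (8.5), differs from that of the centre's majority.

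The cost is protocol wording and one estimate, with no new subjects or data. The sponsor gives up a claim about ethnicity that the design could not support.

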## 5. STUDY DESIGN

### 5.1 Overview

This will be a Phase 2A, two-centre, double-blind, placebo-controlled, multiple-dose study to assess the effect of multiple oral doses of TRC150094 on insulin sensitivity in 40 overweight/obese male subjects. 20 Subjects will be enrolled in India and another 20 subjects at Amsterdam, the Netherlands. The maximum duration of participation in the study for each subject will be 17.5 weeks including a  $\leq 12$  weeks screening period, 4 weeks of treatment and a 10 days post treatment follow-up evaluation period (see Appendix B for Study Assessments).

At each study site 20 subjects will be enrolled. Each subject will attend the study centre in a fasting state, for a screening visit, 2 study visits (one baseline and one end of treatment), 1 intermediate safety visit and 1 post-study follow-up visit (Total 5 visits). The subjects at each site will be randomized to receive TRC150094 or placebo in a ratio of 1:1. The tentative dose level is 50 mg to be administered OD (morning) under fasting conditions. Dosing will take place daily on Days 1–28. Subjects will arrive at the study centre for screening visit. Physical examination, vital signs, safety biochemistry and laboratory investigations for verification of inclusion/ exclusion criteria will be performed during screening visit. Subjects meeting all the inclusion criteria and none of the exclusion criteria and who have given their informed consent for the study will be asked to come for the study on Day 0 (or day -1 if required). Baseline investigations (including baseline clamp procedure and hepatic MRS) will be done on Day 0 (or day -1). Subjects will receive properly labelled bottle containing either Active treatment or Placebo as per the randomization number of the subject. Subjects will be asked to take the dose (tentatively 50mg) OD in the morning on Days 1-28 inclusive, in fasting conditions, with a glass of water. Drug compliance of at least 90% will be ensured. Hence the allowable limit of missing the dose should not be more than 3 days in total. Discontinuation should not be of more than 2 consecutive days at any point of time. Uniformity in timing of intake of medication will be advised which should be preferably within  $\pm 1$  hr of the time of intake of study medication on Day 1. Each subject will attend the study centre on Day 14 for safety investigations. A deviation of  $\pm 1$  day will be allowed for these visits. Subjects will attend the study centre again on Day 28 for clamp procedure and hepatic MRS. A

---

deviation up to +2 days is acceptable only in those cases that missed doses within the limits given above and has continued planned medication up to day of post-dose investigations. For further details, see Section 8.4 and Appendix A. It is planned that the study will take place over 6 months (including screening and follow-up periods).

## **5.2 Rationale for Study Design, Control, Doses and Study Population**

The tentative dose (50 mg) has been selected based on estimates of safety from pre-clinical studies, and safety and tolerability data obtained from SAD study. The study will begin subject to the availability of safety data of relevant dose of MAD study (currently ongoing). A placebo control has been included in the study design to allow for an unbiased assessment of insulin sensitivity. The study will be double-blind and randomized to ensure unbiased data.

## **6. STUDY POPULATION AND TREATMENT**

### **6.1 Number and Description of Subjects**

It is intended that 40 subjects complete the study: 20 subjects in India and 20 subjects in Amsterdam, the Netherlands. An attempt will be made to dose 20 subjects at each study site (10 for Active treatment; 10 for Placebo treatment). Subjects will be identified by their initials. In addition, subjects will be given a screening number at screening and a subject (randomisation) number at the time of randomisation. A list identifying the subjects by initials, screening number, subject number and status (completed study/withdrawn) will be kept in the trial master file.

### **6.2 Inclusion Criteria**

Subjects will be considered eligible for entry in the study if they meet all of the following criteria.

1. Adult male
2. Age range 30–65 years at screening
3. Caucasian or Indian Ethnicity
4. Waist circumference  $\geq 102$  cm for Caucasians and  $\geq 90$  cm for Indians at screening.
5. Fasting Serum Insulin  $\geq 10$  mU/ml at screening
6. Blood Pressure  $\geq 130/85$  mmHg at screening (or patients taking medication for hypertension)
7. Stable weight during 3 months prior to the study (assessed through medical history of the patient)
8. Drug naïve diabetic patients\* or patients with impaired fasting glucose i.e  $> 100$  mg/dl or  $5.5$  mmol/l and  $< 200$  mg/dl or  $11.0$  mmol/l. Diabetic patients who were taking metformin and have undergone washout for at least 4 weeks before Day 0 and are currently on life style modification as a treatment for diabetes will also be allowed in the study
9. Willingness to give written informed consent (prior to any study-related procedures being performed) and ability to adhere to the study restrictions and assessments schedule.

---

**\* Diabetic patient is defined as a patient with a documented history of type II DM or a documented history of a fasting glucose > 200 mg/dl or 11.0 mmol/l or 2x fasting glucose > 126 mg/dl or 6.9 mmol/l (2x = recorded twice)**

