### Methodology

On screening, patients will visit the trial unit after an overnight fast. After informed consent is obtained, subjects will be screened for eligibility to participate in the study. Screening will include a careful assessment of the inclusion/exclusion criteria and collection of blood and urine for screening tests. Subjects will give a full medical history, and undergo a full physical examination, including height, body weight, waist circumference and vital sign measurements. A 12-lead electrocardiogram (ECG) tracing will be obtained to screen for underlying cardiac disease. All subjects will receive life style instructions (normal diet,  $\leq 2$  alcohol consumptions a day, restriction on caffeine and grapefruit intake, no strenuous or unaccustomed exercise). If a patient is on oral metformin treatment, treatment will be discontinued until the end of the study. Subjects who meet all entry criteria will be eligible for randomization on Day 0.

On Day 0 patients will visit the trial unit after an overnight fast. The patients may be asked to present in CRU on Day -1 if required (for baseline investigations). At Day 0 (and/or Day -1), the following assessments will be performed: Physical examination, vital signs, height and body weight, waist circumference, clinical laboratory tests, urine collection (urinalysis), 12-lead ECG, AEs and change in concomitant medications will be reported, hyperinsulinemic euglycemic clamp (the clamp procedure is described in Appendix C) will be performed. Liver fat will be measured by 1H MRS. All patients will get life style instructions.

On day  $14 \pm 1$ , the patients will visit the trial unit after an overnight fast. The following assessments will be performed on day  $14 \pm 1$ : vital signs, height and body weight, waist circumference, safety clinical laboratory tests, urine collection (urinalysis), 12-lead ECG, AEs and change in concomitant medications will be reported, all patients will get life style instructions.

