#### **6.6 Prior and Concomitant Medication**

Subjects are not permitted to enter the study if they have taken any investigational drug in the 3 months prior to study drug administration. Subjects are not permitted to enter the study if they have taken insulin or any oral anti-diabetic (except metformin)

---

---

in past. Those subjects who are taking metformin may be included in the study after a washout of at least 4 weeks. During these 4 weeks, these subjects should be on lifestyle modification as a treatment for diabetes. Other concomitant medications may be allowed after agreement between principal investigator and sponsor. Prior medications (up to 4 weeks prior to the dosing occasion) and all concomitant medications (up to the post-study follow-up visit) will be recorded in the subject's case report form (CRF).

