### **8.5 Study Visits**

#### ***Screening***

Subjects will attend the CRU for a screening visit up to 28 days before their Baseline investigation (Day 0). Prior to attending for a screening visit, subjects will be asked to comply with certain exercise and dietary restrictions, as specified in Section 6.7. Informed consent must be obtained at this visit before any study procedures are performed. Further details regarding informed consent are provided in Section 11.2. A screening log will be kept to record subjects who sign the informed consent form and who are screened. For those subjects who are screen failures, a reason will be documented. The following assessments/information will be performed/ recorded

- date of birth and age
- race

- 
- height and body weight (measured while wearing indoor clothing and no shoes)
  - waist circumference
  - body mass index (BMI), calculated as weight (kg)/height (m)
  - smoking status / intake of tobacco in any other form (including current and historical use of tobacco, and ability to stop smoking / tobacco intake in any other form, for study periods)
  - medical history (any significant conditions or diseases that stopped at or prior to screening)
  - pre-existing (concurrent) conditions (those present at the screening visit)
  - prior and ongoing medication (medications taken up to 4 weeks prior to first dose)
  - full physical examination
  - vital signs (supine and standing) and body temperature
  - 12-lead ECG
  - chest X-ray (to exclude active tuberculosis, in India only)
  - clinical laboratory tests (blood sample for haematology and biochemistry tests; and urine sample for urinalysis)
  - lipid Parameters
  - viral serology (hepatitis B surface antigen [HBsAg], hepatitis C antibody, human immunodeficiency virus [HIV I and HIV II])
  - alcohol breath test
  - urinary drugs of abuse screen (amphetamines, barbiturates, benzodiazepines, cannabinoids, cocaine, opiates and methadone).

Those subjects who are eligible for the study, based on the inclusion and exclusion criteria, will be invited to take part in the study. Lifestyle instructions as mentioned in Section 6.7 will be given.

*Day 0*

---

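### The fasting insulin entry threshold is printed in a unit that is very likely wrong, and sections 5.1 and 8.5 give screening windows of 12 weeks and 28 days that contradict each other

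*Protocol*

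**What the plan says.** **Insulin threshold.** Subjects must meet every inclusion criterion. Criterion 5 in section 6.2 is "Fasting Serum Insulin $\geq 10$ mU/ml at screening", and the synopsis prints the same figure and unit.

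**Screening window.** Section 5.1 gives a maximum participation of "17.5 weeks including a $\leq 12$ weeks screening period, 4 weeks of treatment and a 10 days post treatment follow-up evaluation period". Section 8.5, under Screening, says "Subjects will attend the CRU for a screening visit up to 28 days before their Baseline investigation (Day 0".

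**Metformin.** Criterion 8 in section 6.2 counts the washout of at least 4 weeks back from Day 0. Section 6.6 adds "Those subjects who are taking metformin may be included in the study after a washout of at least 4 weeks". The synopsis, in its paragraph on the screening visit, says "If a patient is on oral metformin treatment, treatment will be discontinued until the end of the study". It gives no length for the screening window.

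**The concern.** The insulin criterion is one of the rules that select an insulin-resistant population, and improving insulin sensitivity is the efficacy part of the primary objective. If the unit is wrong as printed, a site must either depart from the text or reinterpret it. Appendix A lists fasting insulin under biochemistry, and section 8.5.6 sends safety laboratory work to each centre's local laboratory, so the protocol should state the reporting unit correctly.

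The window matters because waist circumference, fasting insulin, blood pressure, eGFR and ALT/AST are all judged at screening (sections 6.2 and 6.3). The two sections allow very different ages for those values at Day 0. The shorter window also meets the washout rule exactly at its edge, so a patient who stops metformin at the screening visit has no scheduling tolerance.

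**Working it through.** **1. Unit conversion.** 10 mU/ml x 1,000 ml/L = 10,000 mU/L.

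**2. Plausibility bound from the clamp.** Section 8.4.1 infuses insulin "for 2hr at a rate of 20mU/m 2 body surface area per min", then "the infusion of insulin is increased to a rate of 60mU/m 2 body surface area per min" from 2 h 15 min. Appendix C stops insulin at 4 h 20 min. The longest times these passages allow are 135 min for step 1 (0:00 to 2:15) and 125 min for step 2 (2:15 to 4:20).

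- Total dose: 20 x 135 + 60 x 125 = 2,700 + 7,500 = 10,200 mU/m2.
- Level if nothing were cleared: 10,200 x body surface / plasma volume.
- Body surface and plasma volume are not in the protocol. The values below are assumptions.

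| Body surface (m2) | Plasma 2.5 L | Plasma 3.0 L | Plasma 3.5 L |
|---|---|---|---|
| 1.7 | 6.94 mU/ml | 5.78 | 4.95 |
| 2.0 | 8.16 | 6.80 | 5.83 |
| 2.3 | 9.38 | 7.82 | 6.70 |
| 2.5 | 10.20 | 8.50 | 7.29 |

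Only one of the twelve combinations reaches 10 mU/ml. The protocol also states 2 h for step 1, and Appendix C shows step 2 as 2:15 to 4:15. With 120 min each, the dose is 20 x 120 + 60 x 120 = 9,600 mU/m2, and the most extreme combination gives 9,600 x 2.5 / 2,500 = 9.6 mU/ml. The clamp is meant to raise insulin above its fasting level, and real clearance is not zero. A fasting value of 10 mU/ml or more is therefore not credible.

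**3. Total participation.** Formula: screening + 4 weeks of treatment + 10/7 weeks of follow-up.

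- With section 5.1's window: 12 + 4 + 1.43 = 17.43 weeks, which reproduces the stated 17.5.
- With section 8.5's window: 4 + 4 + 1.43 = 9.43 weeks, which does not.

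**4. Age of screening values at Day 0.** Up to 12 x 7 = 84 days under section 5.1; at most 28 days under section 8.5.

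**5. Room for a washout begun at the screening visit.** At least 28 days are needed before Day 0.

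- 28-day window: 28 - 28 = 0 days of slack, so Day -28 is the only screening day that works.
- 84-day window: 84 - 28 = 56 days of slack, so 57 screening days work (Day -84 to Day -28).

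**The case against.** **The unit may be a reading artefact.** A Greek letter seems to have been lost before the word oxidation in the Introduction, so the printed milli prefix could be a lost micro sign. This stands as a reason to check the source first; if a micro sign is there, the insulin point falls away. Against it, micro signs survive in sections 6.4 and 8.4.1, and both printings of criterion 5 carry the same unit.

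**A reader might infer that the threshold is a thousandfold out of reach, or that the clamp proves it unattainable.** Neither follows. The factor of 1,000 is the ratio between the printed unit and an assumed intended one, and the protocol gives no reference fasting insulin value. The clamp bound rests on assumed body size and plasma volume, and its upper end touches 10 mU/ml. What it supports is implausibility.

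**A reader might infer that the 28-day window is incompatible with the washout.** It is not: 28 days is exactly 4 weeks, and criterion 8 admits patients who have already completed a washout. What remains is the lack of slack for a patient still on metformin at screening. Consent is taken at that visit and must precede study procedures, so such a patient would not ordinarily begin a trial washout sooner.

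**A reader might infer that the window cannot be applied, or that it biases the treatment comparison.** The window is a visit-timing rule, and screening within 28 days satisfies both sections. Randomisation is 1:1 within each site, and vital signs, waist, weight, laboratory tests and the clamp are all done at Day 0, so the efficacy baselines are not old. Nor does the discrepancy relax the washout: shortening it would breach criterion 8 and section 6.6. Nothing in the protocol shows that the two sites would adopt different windows.

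**Conclusion.** Two faults in operative text stand.

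- **Insulin unit.** The threshold of 10,000 mU/L, as printed, is implausible for a fasting subject. It compares with 5.0 to 10.2 mU/ml from the whole clamp dose with no clearance, under assumed ranges of 1.7 to 2.5 m2 and 2.5 to 3.5 L. The unit is very likely wrong. That mU/L (the same as microU/ml) was intended is an assumption, and the finding is conditional on the source file showing the same unit.
- **Screening window.** Sections 5.1 and 8.5 contradict each other, 84 days against 28, and only the longer window agrees with the 17.5-week maximum. The effect is on how old the eligibility values may be and on the zero slack for patients stopping metformin at screening. Patients already washed out are unaffected. The documents do not support a claim of bias between active and placebo.

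**What to change.** Check criterion 5 against the source file. If the unit is as printed, the sponsor should confirm the intended unit, correct it in the synopsis and section 6.2, and use it in the eligibility check of the eCRF that the Amsterdam unit prepares for both sites (section 10.2).

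Reconcile section 5.1, section 8.5, the synopsis screening paragraph, criterion 8 and section 6.6 to one screening window consistent with the stated washout and the stated maximum duration. The choice of window and washout is the sponsor's. If the 12-week window is kept, 17.5 weeks already agrees with it; if the 28-day window is kept, the maximum must be restated.

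The cost is a few text corrections and one eCRF check, with no added visits or procedures.
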